##### 5.11.3.5.3 Causality

The investigator must assess the causality of all serious events in relation to the trial therapy using the definitions in Table 2.

**Table 2: Causality definitions**

| Relationship | Description | Event type |
| --- | --- | --- |
| Unrelated | There is no evidence of any causal relationship | Unrelated SAE |
| Unlikely to be related | There is little evidence to suggest that there is a causal relationship (eg the event did not occur within a reasonable time after administration of the trial intervention). There is another reasonable explanation for the event (eg the participant’s clinical condition or other concomitant treatment) | Unrelated SAE |
| Possibly related | There is some evidence to suggest a causal relationship (eg because the event occurs within a reasonable time after surgery). However, the influence of other factors may have contributed to the event (eg the participant’s clinical condition or other concomitant treatment) | Related SAE |
| Probably related | There is evidence to suggest a causal relationship and the influence of other factors is unlikely | Related SAE |
| Definitely related | There is clear evidence to suggest a causal relationship and other possible contributing factors can be ruled out. | Related SAE |

##### 5.11.3.5.4 Expectedness

If there is at least a possible involvement of the trial intervention (including any comparators), the investigator and sponsor must assess the expectedness of the event. An unexpected adverse event is one that is not reported in the current literature, or one that is more frequently reported or more severe than previously reported. See below for a list of expected complications associated with the procedures being used in this trial.

Expected intraoperative complications for **both** arms include all those common to phacoemulsification cataract surgery:(2)

- Anterior capsule tear
- Posterior capsule tear with or without vitreous loss
- Choroidal effusion/ haemorrhage
- Zonular Dialysis
- Intra-operative pupil constriction needing intervention
- Dropped lens fragments or nucleus

Expected trial complications specifically for the **laser assisted** arm:

- Failure to dock to laser
- Aborted or incomplete laser delivery
- Incomplete capsulotomy identified in surgery, requiring manual completion
- Laser delivery to Inappropriate structure of eye

Expected post-operative complications for **both** arms:

- Post-operative uveitis
- Endophthalmitis
- Macular oedema
- Retinal tear or retinal detachment
- Elevated intraocular pressure requiring treatment
- Medication allergy or intolerance
- Corneal oedema
- Vitreous to wound
- Other ocular surgery

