### 5.11.3 Data Monitoring for Harm

#### 5.11.3.1 Safety reporting

Definitions of harm of the EU Directive 2001/20/EC Article 2 based on the principles of ICH GCP apply to this trial.

Table 2: Adverse Event Definitions

| **Adverse Event (AE)** | Any untoward medical occurrence in a study participant which does not necessarily have a causal relationship with the treatment under study e.g. abnormal laboratory findings, unfavourable symptoms or diseases. |
| --- | --- |
| **Serious Adverse Event (SAE)** | Any AE that :   - results in death - is life threatening* - requires hospitalisation or prolongs existing hospitalisation** - results in persistent or significant disability or incapacity - is a congenital anomaly or birth defect - or is another important medical condition*** |
| **Suspected Unexpected Serious Adverse Event** | A serious adverse event, the nature or severity of which **is not consistent** with the known potentially **expected** events associated with the applicable trial treatment. The event is evaluated as having a possible, probable or definite relationship to a trial treatment **and** is unexpected for that trial treatment. |
| * the term life threatening here refers to an event in which the patient is at risk of death at the time of the event; it does not refer to an event that might hypothetically cause death if it was more severe (eg a silent myocardial infarction)  ** Hospitalisation is defined as an in-patient admission, regardless of length of stay, even if the hospitalisation is a precautionary measure for continued observation. Hospitalisation for pre-existing conditions (including elective procedures that have not worsened) do not constitute an SAE  *** Medical judgement should be exercised in deciding whether an AE is serious in other situations. | |

Adverse events include:

- an exacerbation of a pre-existing illness
- an increase in the frequency or intensity of a pre-existing episodic event or condition
- a condition (regardless of whether PRESENT prior to the start of the trial) that is DETECTED after surgery. (This does not include pre-existing conditions recorded as such at baseline.)
- continuous persistent disease or a symptom present at baseline that worsens following surgery

Adverse events do NOT include:

- Medical or surgical procedures: the condition that leads to the procedure is the adverse event
- Pre-existing disease or a condition present before treatment that does not worsen

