#### 5.11.3.6 Notifications

##### 5.11.3.6.1 Notifications by the Investigator to CCTU

CCTU must be notified of all SAEs immediately but not later than 24 hours of the investigator becoming aware of the event.

Investigators should notify CCTU of any SAEs and other Notifiable Adverse Events (NAEs) occurring from the time of randomisation until 12 months following surgery for all participants.

The SAE form must be completed by the investigator (the consultant named on the delegation of responsibilities list who is responsible for the participant’s care) or clinical delegate, with attention paid to the grading, causality and expectedness of the event. In the absence of the responsible investigator, the SAE form should be completed and signed by a member of the site trial team and emailed as appropriate within the timeline. The responsible investigator should check the SAE form at the earliest opportunity, make any changes necessary, sign and then email to CCTU. Detailed written reports should be completed as appropriate. Systems will be in place at the site to enable the investigator to check the form for clinical accuracy as soon as possible.

The minimum criteria required for reporting an SAE are the trial number and date of birth, name of reporting investigator and sufficient information on the event to confirm seriousness. Any further information regarding the event that is unavailable at the time of the first report should be sent as soon as it becomes available.

The SAE form and any follow-up forms must be scanned and sent to UCL CCTU in an encrypted format. Details of the method of transfer will be given at the Site Initiation Visit and documented in the Safety Management Plan. Participants must be followed up until clinical recovery is complete and laboratory results have returned to normal or baseline values, or until the event has stabilised. Follow-up should continue after completion of protocol treatment and/or trial follow-up if necessary. Follow-up SAE forms (clearly marked as follow-up) should be completed and sent to CCTU as further information becomes available. Additional information and/or copies of test results etc may be provided separately. The participant must be identified by trial number, date of birth and initials only. The participant’s name should not be used on any correspondence and should be blacked out and replaced with trial identifiers on any test results.

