##### 5.11.3.6.2 CCTU responsibilities

The Chief Investigator (CI or a medically qualified delegate) will review all SAE reports received. In the event of disagreement between the causality assessment given by the local investigator and the CI, both opinions and any justifications will be provided in subsequent reports.

The delegated staff at CCTU will review the assessment for expectedness and, after discussion with the CI, may over-rule the local investigator assessment of expectedness for the purposes of onward reporting.

CCTU is undertaking the duties of trial sponsor and is responsible for the reporting of related unexpected SAEs to the REC as appropriate. Individual SAEs that are related and unexpected must be reported to the REC within 15 days of the Chief Investigator becoming aware of the event. Fatal and life threatening Serious Unexpected Adverse Events must be reported to the REC within 7 days of UCL CCTU becoming aware of the event; other Serious Unexpected Adverse Events must be reported within 15 days.

CCTU will keep investigators informed of any safety issues that arise during the course of the trial.

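### An unspecified procedure, other ocular surgery, stands on the list of expected complications, so a related serious condition that ends in re-operation can be classed as expected

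*Protocol*

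**What the plan says.** Section 5.11.3.5.4 (Expectedness) first gives a general test: "An unexpected adverse event is one that is not reported in the current literature, or one that is more frequently reported or more severe", the comparison being with earlier reports. It then points the assessor to a reference list: "See below for a list of expected complications associated with the procedures being used in this trial". The post-operative part of that list, which applies to both arms, has nine entries. Eight are conditions or findings, such as endophthalmitis, macular oedema and retinal detachment. The ninth is "Other ocular surgery".

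Section 5.11.3.1 (Safety reporting) puts the following among the things that are not adverse events: "Medical or surgical procedures: the condition that leads to the procedure is the adverse event".

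Section 5.11.3.6.2 (CCTU responsibilities) makes expectedness part of the trigger for onward reporting: "Individual SAEs that are related and unexpected must be reported to the REC within 15 days" of the Chief Investigator learning of them. Fatal and life-threatening unexpected serious events have a 7-day limit.

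Section 5.11.3.6.1 asks sites to notify CCTU of serious adverse events from randomisation until 12 months after surgery. Its closing paragraph continues notification to trial closure, but only for serious events that are unexpected.

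**The concern.** Expectedness decides whether a related serious event gets an individual report to the REC. The reference list for that decision should therefore hold the same kind of thing as the events being judged. Here one entry is a treatment, and the protocol's own definitions say that a treatment is not an event. It is also open-ended: it names no operation, no reason for operating and no degree of severity.

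At stake is the consistency of safety reporting for a device whose rationale (section 4.1) rests partly on the lack of well-designed randomised evidence on safety. A harm that nobody anticipated is what expedited reporting exists to catch, and some such harms would be treated by a further operation.

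**Working it through.** There is no figure to reproduce. The check is to set the sections side by side and ask when the line changes a classification.

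**Step 1: what is being judged.** Under section 5.11.3.1 the event is the condition that led to the operation. The complication outcome in section 5.5.2 points the same way: a complication is an event that may require further treatment, so the treatment is not itself the complication.

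**Step 2: three kinds of related serious condition treated by further eye surgery.**

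| Condition | Judged on the condition | Matched to the line | Does the line matter? |
| --- | --- | --- | --- |
| Already on the list (e.g. retinal detachment, dropped nucleus) | Expected, unless more frequent or more severe than reported | Expected | No; the condition's own entry already covers it |
| Not listed, but in the literature at similar frequency and severity | Not unexpected under the general test | Expected | No |
| Not listed, and either absent from the literature or more frequent or more severe than reported | Unexpected | Expected | Yes; the two readings are opposite |

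The line is therefore redundant in the first two rows. In the third it conflicts with both section 5.11.3.1 and the general test in its own section.

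**Step 3: what follows in the third row.** Section 5.11.3.6.2 requires an individual REC report only for events that are both related and unexpected. If the event is marked expected, the 7- or 15-day report is no longer required. The definition of a suspected unexpected serious event in section 5.11.3.1 gives no independent check, because it too asks whether the event is consistent with the known expected events.

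**Step 4: after 12 months.** Up to 12 months after surgery, all serious events go to CCTU whatever their expectedness. From then to trial closure, only unexpected ones must. Section 5.6.4 sets closure no earlier than the last participant's 12-month visit, and section 5.8.1 plans 18 months of recruitment. If recruitment ran to plan and the wait for surgery were similar throughout, the earliest participants would spend up to about 18 months in this later window and the latest almost none. In that window, an event marked expected on the strength of the line need not reach CCTU, so the central review would not see it.

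**The case against.** The strongest reply is that a site has to misapply the protocol before anything is lost. Section 5.11.3.1 tells it to assess the condition, and the general test in section 5.11.3.5.4 makes a condition that is new to the literature unexpected. Further checks follow:

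- "CCTU must be notified of all SAEs immediately but not later than 24 hours" of the investigator becoming aware, expected or not.
- Section 5.11.3.5.4 has the sponsor as well as the investigator assess expectedness.
- Under section 5.11.3.6.2 the Chief Investigator or a delegate reviews every serious event report. CCTU staff review the expectedness assessment and "may over-rule the local investigator assessment of expectedness for the purposes of onward reporting".
- The data monitoring committee receives safety reports (section 5.11.2), and general safety reports go to the REC (section 6.2).

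Most of this stands and it limits the point. It does not remove it. The list is the only reference list that the protocol gives, and the central reviewer works from the same one. The review is mandatory but the over-rule is discretionary. Committee and general reports do not replace an individual report with a time limit, and the 24-hour rule covers all serious events only to 12 months.

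Three stronger readings might be inferred, and the documents do not support them.

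- *That such events escape all reporting, or that the line switches off expedited reporting for every re-operation.* Only the individual expedited report, and notification to CCTU after 12 months, are at risk. A re-operation is also not serious by itself: hospitalisation means in-patient admission (section 5.11.3.1), and the trial runs in day surgery units (section 5.1.1).
- *That the size can be read from the capsule rupture figures in section 4.1.* Applying them gives 808 × 0.019 = 15.4 cases, and 15.4 ÷ 5 = 3.1 needing further surgery. These cases do not measure the problem. Posterior capsule tear and dropped lens fragments are themselves on the expected list, so deleting the line would not reclassify them. Rupture with vitreous loss is also notifiable within 48 hours (section 5.11.3.3).
- *That the data monitoring committee or the complications outcome would lose the underlying cause.* Complications are taken from the medical notes (section 5.9.2) under the definition in section 5.5.2. Neither depends on the expectedness list.

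**Conclusion.** The inconsistency is real. One entry on the expected list is something that the protocol says is not an adverse event, and the same related serious event can be called expected or unexpected according to which section the assessor follows. The line makes a difference only for conditions that are not listed, are related and serious, are treated by further eye surgery, and would be unexpected on their own merits. For these it can remove the individual 7- or 15-day REC report and, after 12 months, the required notification to CCTU.

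The protocol gives no rate for this group, so the number of events cannot be estimated and may be small. The conclusion assumes that an assessor takes the line literally and, for events within 12 months, that central review does not correct the classification. The primary outcome, sample size and efficacy analysis are not affected. This is a modest fault in safety reporting, worth correcting because the correction is simple.

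**What to change.** Delete "Other ocular surgery" from the expected list in section 5.11.3.5.4. Add one sentence there: where further ocular surgery takes place, expectedness is judged on the condition that led to it, in line with section 5.11.3.1. If the line was meant to cover particular known conditions, name those conditions. Any event already classed as expected only because of this line should be reassessed.

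The cost is one deleted line and one added sentence, handled under the amendment process in section 6.4, and possibly a few more expedited REC reports. No treatment, visit, endpoint or analysis changes.

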#### 5.11.3.6 Notifications

##### 5.11.3.6.1 Notifications by the Investigator to CCTU

CCTU must be notified of all SAEs immediately but not later than 24 hours of the investigator becoming aware of the event.

Investigators should notify CCTU of any SAEs and other Notifiable Adverse Events (NAEs) occurring from the time of randomisation until 12 months following surgery for all participants.

The SAE form must be completed by the investigator (the consultant named on the delegation of responsibilities list who is responsible for the participant’s care) or clinical delegate, with attention paid to the grading, causality and expectedness of the event. In the absence of the responsible investigator, the SAE form should be completed and signed by a member of the site trial team and emailed as appropriate within the timeline. The responsible investigator should check the SAE form at the earliest opportunity, make any changes necessary, sign and then email to CCTU. Detailed written reports should be completed as appropriate. Systems will be in place at the site to enable the investigator to check the form for clinical accuracy as soon as possible.

The minimum criteria required for reporting an SAE are the trial number and date of birth, name of reporting investigator and sufficient information on the event to confirm seriousness. Any further information regarding the event that is unavailable at the time of the first report should be sent as soon as it becomes available.

The SAE form and any follow-up forms must be scanned and sent to UCL CCTU in an encrypted format. Details of the method of transfer will be given at the Site Initiation Visit and documented in the Safety Management Plan. Participants must be followed up until clinical recovery is complete and laboratory results have returned to normal or baseline values, or until the event has stabilised. Follow-up should continue after completion of protocol treatment and/or trial follow-up if necessary. Follow-up SAE forms (clearly marked as follow-up) should be completed and sent to CCTU as further information becomes available. Additional information and/or copies of test results etc may be provided separately. The participant must be identified by trial number, date of birth and initials only. The participant’s name should not be used on any correspondence and should be blacked out and replaced with trial identifiers on any test results.

UCL CCTU must be notified of all Serious Unexpected Adverse Events within 24 hours of the investigator becoming aware of the event and must be notified to UCL CCTU until trial closure.

##### 5.11.3.6.2 CCTU responsibilities

The Chief Investigator (CI or a medically qualified delegate) will review all SAE reports received. In the event of disagreement between the causality assessment given by the local investigator and the CI, both opinions and any justifications will be provided in subsequent reports.

The delegated staff at CCTU will review the assessment for expectedness and, after discussion with the CI, may over-rule the local investigator assessment of expectedness for the purposes of onward reporting.

CCTU is undertaking the duties of trial sponsor and is responsible for the reporting of related unexpected SAEs to the REC as appropriate. Individual SAEs that are related and unexpected must be reported to the REC within 15 days of the Chief Investigator becoming aware of the event. Fatal and life threatening Serious Unexpected Adverse Events must be reported to the REC within 7 days of UCL CCTU becoming aware of the event; other Serious Unexpected Adverse Events must be reported within 15 days.

CCTU will keep investigators informed of any safety issues that arise during the course of the trial.

### 5.11.4 Quality Assurance and Control

#### 5.11.4.1 Risk Assessment

The Quality Assurance (QA) and Quality Control (QC) considerations for the **FACT** trial are based on the standard CCTU Quality Management Policy that includes a formal Risk Assessment, and that acknowledges the risks associated with the conduct of the trial and proposals of how to mitigate them through appropriate QA and QC processes. Risks are defined in terms of their impact on: the rights and safety of participants; project concept including trial design, reliability of results and institutional risk; project management; and other considerations.

QA is defined as all planned and systematic actions established to ensure the trial is performed and data generated, documented and/or recorded and reported in compliance with the principles of GCP and applicable regulatory requirements. QC is defined as the operational techniques and activities performed within the QA system to verify that the requirements for quality of the trial related activities are fulfilled.

#### 5.11.4.2 Central Monitoring at CCTU

CCTU staff will review Case Report Form (CRF) data for errors and missing key data points. The trial database will also be programmed to generate reports on errors and error rates. Essential trial issues, events and outputs, including defined key data points, will be detailed in the **FACT** trial Data Management Plan.

#### 5.11.4.3 On-site Monitoring

The frequency, type and intensity of routine and triggered on-site monitoring will be detailed in the **FACT** Quality Management and Monitoring Plan (QMMP). The QMMP will also detail the procedures for review and sign-off of monitoring reports. In the event of a request for a trial site inspection by any regulatory authority UCL CCTU must be notified as soon as possible.

##### 5.11.4.3.1 Direct access to participant records

Participating investigators must agree to allow trial related monitoring, audits, REC review and regulatory inspections, by providing access to source data and other trial related documentation as required. Participant consent for this must be obtained as part of the informed consent process for the trial.

#### 5.11.4.4 Trial Oversight

Trial oversight is intended to preserve the integrity of the trial by independently verifying a variety of processes and prompting corrective action where necessary. The processes reviewed relate to participant enrolment, consent, eligibility, and allocation to trial groups; adherence to trial interventions and policies to protect participants, including reporting of harms; completeness, accuracy and timeliness of data collection; and will verify adherence to applicable policies detailed in the Compliance section of the protocol. Independent trial oversight complies with the CCTU trial oversight policy.

In multi-centre trials this oversight is considered and described both overall and for each recruiting centre by exploring the trial dataset or performing site visits as described in the **FACT** Quality Management and Monitoring Plan.

